## Abstract

**Introduction:**

Current dietary assessment methods struggle to accurately capture individuals’ dietary habits. The ‘Standardised and Objective Dietary Intake Assessment Tool’ (SODIAT)-1 study aims to assess the effectiveness of three emerging technologies (urine and capillary blood biomarkers, wearable camera technology) and two online self-reporting dietary assessment tools to monitor dietary intake.

**Methods:**

This randomised controlled crossover trial was conducted at two sites (Hammersmith Hospital and the University of Reading) and aimed to recruit 30 UK participants (aged 18-70 years, BMI 20-30 kg/m
^2^). Exclusion criteria included recent weight change, food allergies/intolerances, restrictive diets, certain health conditions and medication use. Volunteers completed an online screening questionnaire via REDCap and eligible participants attended a pre-study visit. Participants consumed, in a random order, two highly-controlled diets (compliant/non-compliant with UK guidelines) for four consecutive days, separated by at least one-week. Dietary intake was monitored daily using wearable cameras and self-recorded using Intake24 (24HR). Two versions of the online eNutri FFQ were completed: at baseline to assess habitual diet and on day 4 of each test period to record food intake. Urine and capillary blood samples were collected for biomarker analysis. Data analysis will assess dietary reporting accuracy across these methods using Lin’s concordance correlation coefficient.

**Discussion and ethical considerations:**

The SODIAT project introduced a novel approach to dietary assessment, aiming to address the limitations like misreporting and inclusivity. However, challenges persist, such as variability in biomarker data due to failure to follow sample storage requirements and the practicalities of wearing cameras throughout the day. To protect privacy, participants removed cameras at inappropriate times, and AI removed non-food related images and blurred faces/device screens captured on the images. The accuracy of the tools in a highly-controlled setting will be evaluated in this study. Future studies are planned to validate these tools further in free-living and minority populations.

## Introduction

Optimal nutrition is fundamental for maintaining good health and preventing diseases across the life course.
^
1
^ The relationship between dietary habits and noncommunicable diseases (NCDs) is globally recognised,
^
2,
3
^ and evidence suggests unhealthy diets are strongly associated with increased prevalence of diabetes, various forms of cancer, and cardiovascular diseases.
^
4–
6
^ The impact of diet on population health has been highlighted by the Global Burden on Disease study that reported over 11 million deaths worldwide per year can be attributed to suboptimal diets.
^
7
^

Nutrition research has a significant role in reducing the detrimental health impact of poor diets globally. Assessing population food intake can provide substantial data on the nation’s nutritional status and may be used in planning and implementation of evidence-based public health interventions.
^
8
^ However, lack of accurate dietary assessment measures continuously undermines the strength and efficacy of public health strategies.
^
9,
10
^ Traditional subjective methods of dietary assessment, such as food frequency questionnaires (FFQs), 24-hour dietary recalls, and food diaries, are widely used to capture individuals’ dietary information.
^
11
^ Despite being non-invasive, easy to use and suitable for large scale studies (depending on method), these self-reporting methods face notable challenges that can compromise the accuracy and reliability of collected dietary data.
^
12–
15
^ Memory recall bias is a common challenge, as participants may struggle to remember all consumed items, leading to potential underreporting or inaccuracies,
^
14
^ whereas social desirability bias occurs when respondents align their reported food choices with perceived societal expectations, impacting the representation of true dietary habits.
^
16
^ In addition, estimating portion sizes poses a challenge, as individuals may struggle with accuracy and perceptions of portion sizes differ between individuals (e.g., small, medium and large).
^
17
^ Finally, response burden and fatigue, particularly prevalent when individuals weigh and record their dietary consumption over extended periods, can result in incomplete records, whereas day-to-day variability in dietary habits (such as oily fish and alcohol that are not typically eaten daily) may not be adequately captured for shorter recording periods.
^
9
^

Cultural and social influences, lack of standardisation in reporting procedures, and limited detail on food preparation methods further contribute to the complexity of self-reported dietary assessments.
^
13
^ The phenomenon of underreporting or overreporting in dietary assessments adds another layer of complexity, for example, individuals with obesity, particularly women, are most likely to underestimate their energy intake by under-reporting high energy foods considered socially undesirable.
^
18
^ Mitigating these challenges and improving accuracy is essential for advancing the assessment methodology of population food intake.
^
14
^

In addition to subjective measures, objective methods can also be used to assess dietary intake. These do not rely on participants’ self-reported intakes, instead dietary intake is assessed using various physical, biochemical, physiological or environmental measures, such as direct observation, nutritional biomarkers and duplicate diets.
^
12
^ The development of advanced technologies, such as sensor-based and image-based tools, has increased the possibilities to address the limitations of self-reporting in nutrition research.
^
19
^ Additionally, detecting dietary biomarkers in bodily fluids can reflect food intake and complement traditional dietary assessment methods.
^
20
^ Implementing these methods minimise the biases associated with subjective measures, however, each objective method has its own limitations, requires the will of participants to comply (e.g., collect samples, wear cameras) and there is no universally accepted “gold standard”.
^
12
^

To address this problem, the ‘Standardised and Objective Dietary Intake Assessment Tool’ (‘
SODIAT’)-1 study will explore the ability of three emerging objective technologies and two subjective online tools to accurately assess what people eat and drink. The objective measures include: 1. Urine biomarker metabolomics,
^
21
^ 2. Capillary blood biomarkers
^
22
^ and 3. Wearable camera technology,
^
23
^ and the subjective measures include eNutri (online FFQ tool)
^
24
^ and Intake24 (online 24h recall tool).
^
13,
24,
25
^ While each tool has been used in nutrition research individually, it is their integration and collective use to enhance reporting accuracy that make this approach novel. The primary objective of the study is to calibrate the above dietary assessment technologies and tools for effectiveness to monitor exposure to foods/food groups commonly consumed in the UK in a controlled diet intervention. By conducting a comprehensive evaluation of their capabilities in accurately reporting dietary intake, the study aims to identify the most promising features of each technology. Subsequently, the research team will collaboratively integrate these features to create a combined optimal tool that maximises accuracy and usability which will be tested in future studies in the home environment (not described in this protocol).

## Methods

### Study population

In randomised cross over study SoDiat-1 thirty male and female participants aged between 18-70 years were recruited by the research teams at Imperial College London and University of Reading, with an equal distribution per study location. Participants of all ethnicities with a body mass index (BMI) 20-30 kg/m
^2^ were eligible. Exclusion criteria were as follows:
•Involvement in any other study during the previous 12 weeks, is unable to commit to the study (e.g., travel commitments) or unwilling to collect urine and blood samples and wear the micro-camera.•A weight change of more than 3kg in the preceding 3 months or following a weight-loss
diet.•Excess alcohol intake (more than 21 alcohol units per week).•Unwilling to abstain from drinking alcohol and avoid strenuous exercise during the two 5-day test periods.•Unwilling to follow the study menus (e.g., dislike of food items, following a restrictive/specialised diet or receiving specialised dietary advice for a medical condition).•Unable to eat fish and/or meat (e.g., are vegan or vegetarian).•Allergy/intolerance to any of the food items in the menu.•Use of dietary supplements (e.g., multivitamins, fish oils), unless willing to have a washout of at least 2 weeks prior to taking part in the study.•Pregnant or lactating.•Diagnosed with any of the following: eating disorder, diabetes, cancer, gastrointestinal disorders (e.g., inflammatory bowel disease or irritable bowel syndrome), kidney disease, liver disease, pancreatitis, HIV or AIDS or any other chronic illness.•Taking any of the following medications: anti-inflammatory drugs or steroids, antibiotics, androgens, phenytoin, erythromycin, or thyroid hormones.•Illicit substance use.•Diagnosed with dementia or other conditions affecting memory.•Difficulty using laptops/tablets (e.g., cannot use these devices without assistance, are blind or have other conditions affecting sight, or have physical disabilities/conditions that affect ability to press buttons).•Cannot read and understand English.

### Recruitment

Various methods of recruitment were employed, including distributing posters around the university campuses, emails sent to the respective clinical unit’s volunteer databases and university mailing lists, and social media advertisements for groups within the universities and surrounding areas. Recruitment started in December 2023 and finished in May 2024, when required sample size was achieved. Recruitment materials included a link and QR code that took interested participants to REDCap, a secure web application for administering online surveys and recording datasets in research studies (
https://www.project-redcap.org/), where they could view and download the participant information sheet.

### Study design

Screening

Interested participants completed an online screening questionnaire on REDCap, after which the respective research teams determined their eligibility and/or requested further information from the interested volunteers.

Consent and pre-study visit

Prior to starting the study, participants attended the NIHR Imperial Clinical Research Facility at Hammersmith Hospital or the Hugh Sinclair Unit of Human Nutrition (HSUHN) at the University of Reading (depending on their preferred location as specified on the screening form). Researchers explained the study in full, reconfirmed eligibility (such as ensuring all food items on the menu can be consumed) and allowed the participant to ask questions before informed written consent was taken. During the pre-study visits, participants were provided with a study handbook and the technologies used during the study were explained and demonstrated to them. Their self-reported BMI was also confirmed by measuring height and weight using a bioelectrical impedance analyser (Tanita MC780 MA P (Imperial) and BC-418 (Reading), TANITA UK Ltd, UK) to ensure the participant was within the correct BMI range. If the volunteer was happy to proceed, they were invited to schedule the two 4-day study visits. They were also provided with urine kits to take home and a reminder checklist/log form for the evening/morning prior to their first visit. A schematic diagram (
Figure 1) illustrates the study process from recruitment through to completion.

**Figure 1. f1:**
[figure not shown]
A schematic diagram of SoDiat Study-1.

### Randomisation

After the pre-study visit, participants were assigned a study ID code and randomisation was undertaken using REDCap. Participants were randomly allocated to one of two diet orders: Diet 1 followed by Diet 2 or Diet 2 followed by Diet 1. Randomisation was stratified by study centres. The research team and participant was not be blinded to the randomisation, as study menus were provided in advance, making it clear which diet they would follow each week.

### Study diets

Participants consumed two controlled diets, one per study period, provided in a random order: Diet 1: non-compliant with UK dietary guidelines (e.g., high in saturated fat, free sugars, and salt and low in fibre); Diet 2: compliant with UK dietary guidelines, e.g., within the dietary reference values for saturated fat (≤10% total energy (TE)), free sugars (≤5 %TE), salt (≤6 g/d) and fibre (≥30 g/d) (
Table 1). The diets were matched for energy, protein, total fat and carbohydrate. Foods and drinks selected for each diet were selected to allow investigation of specific biomarkers.
^
21
^ Each diet consisted of a 2-day repeating menu (e.g., menu A served on days 1 and 3, and menu B served on days 2 and 4) as shown in
Tables 2 and
3. Bottled spring water was also be available to drink throughout the day. Meals and snacks were consumed at 2-hour intervals throughout the study days (9 am breakfast, 11 am morning snack, 1 pm lunch, 3 pm afternoon snack, and 5 pm dinner) and were served using identical tableware at each research unit (white crockery and clear glass on days 1 and 2 and patterned crockery and coloured glass on days 3 and 4); no foods/drinks were consumed directly from their packaging. Participants were also provided with a snack and bottled water to take home to consume before 8 pm and instructed not to eat or drink anything else before returning to the research unit the following day.

**Table 1. T1:** Nutrient composition of the study diets
*.

Nutrient	Diet A	Diet B
Energy (kcal/d)	2291	2168
Protein (%TE)	14.8	14.3
Total fat (%TE)	35.6	35.6
Saturated fat (%TE)	16.4	5.7
Carbohydrates (%TE)	46.8	43.5
Free sugars (%TE)	13.6	4.6
Dietary fibre (AOAC) (g/d)	21.8	38.8
Salt (g/d)	7.6	5.6

* Mean of menu 1 and menu 2 per study diet.

**Table 2. T2:** Study menus for diet 1.

Menu	Menu items and quantities
**Menu A**	
**Breakfast**	Pain au chocolat (chocolate filled pastry) (45g)
	Honey nut cornflakes (30g) with whole milk (200g)
	Tea (245g) with whole milk (25g) and sugar (5g)
**Morning snack**	Cheese-flavoured crackers (23g)
	Instant coffee (230g) with whole milk (40g) and sugar (5g)
**Lunch**	Pepperoni, ham and mushroom pizza baguettes (250g)
**Afternoon snack**	Chocolate-coated caramel wafer bar (30g)
	Chocolate-flavoured milkshake mix (20g) with whole milk (250g)
**Dinner**	Beef lasagne ready meal (400g) with frozen mixed vegetables (carrots, peas and green beans) (68g)
	Apple and raspberry juice drink (250g)
**Evening snack**	Salt and vinegar potato crisps (25g)
**Menu B**	
**Breakfast**	White bread toasted (80g) with spreadable butter (20g)
	Baked beans and pork sausages canned in tomato sauce (208g)
	Tea (245g) with whole milk (25g) and sugar (5g)
**Morning snack**	Coconut macaroon (chewy coconut ‘biscuit’) (30g)
	Instant coffee (230g) with whole milk (40g) (no sugar)
**Lunch**	Chicken and bacon pasta in a creamy sauce ready meal (400g)
**Afternoon snack**	Ready salted potato crisps (18g)
	Fizzy orange drink (330g)
**Dinner**	Beef stroganoff in a creamy mushroom sauce with rice ready meal (400g) with frozen mixed vegetables (carrots, broccoli and sweetcorn) (68g)
	Apple juice (200g)
**Evening snack**	Chocolate covered wafer biscuit bar (32g)

**Table 3. T3:** Study menus for diet 2.

Menu	Menu items and quantities
**Menu A**	
**Breakfast**	Muesli with dried fruits (50g) and unsweetened soya drink (200g)
	Wholemeal seeded bread toasted (50g) with peanut butter (25g)
	Tea (240g) with skimmed milk (30g)
**Morning snack**	Dried apple rings (30g)
	0% fat Greek style flavoured yogurt (115g)
	Instant coffee (220g) with skimmed milk (50g)
**Lunch**	Chicken and pasta in a spicy tomato sauce ready meal (400g) with frozen mixed vegetables (carrots, broccoli and sweetcorn (68g)
	Mandarins in juice (113g)
**Afternoon snack**	Reduced salt green pitted olives (30g), cherry tomatoes (75g) and breadsticks (20g)
**Dinner**	Vegetable Biryani (mildly spiced mixed roasted vegetables with basmati rice) ready meal (400g)
	Onion bhaji (50g)
**Evening snack**	Reduced salt potato crisps (25g)
**Menu B**	
**Breakfast**	Weetabix (38g) with hazelnuts (15g), frozen blueberries (80g) and oat drink (120g)
	Wholemeal bread toasted (44g) with sunflower spread (10g)
	Tea (240g) with skimmed milk (30g)
**Morning snack**	Peaches in juice (113g) & whole almonds (30g)
	Coffee (220g) with skimmed milk (50g)
**Lunch**	Moroccan spiced chicken and chickpea soup (300g) with wholemeal bread roll (54g) and sunflower spread (15g) Red grapes (80g)
**Afternoon snack**	Houmous dip (50g) with lightly salted tortilla chips (30g) Sugar-free lemonade (330g)
**Dinner**	Salmon pie (salmon in a cream sauce topped with mashed potato and cheese) ready meal (375g) with frozen mixed vegetables (carrots, peas and green beans) (68g)
	Fruit flavoured water drink with sweeteners (250g)
**Evening snack**	Dried fruit and nut chewy bar (30g)

### Study visits

The study visits took place at the NIHR/Imperial Clinical Research Facility at Hammersmith Hospital or the HSUHN at the University of Reading and included two study periods each consisting of four full-day (8 am to 6 pm) visits from Monday to Thursday with a short visit on the fifth study day (Friday) to return final urine samples and all study equipment. A washout period of at least one week between study periods was required (menstruating women attended study visits at the same phase of their menstrual cycle).

### Study visit procedures

The day before starting each study period, participants were asked to restrict their caffeine and alcohol intakes and exercise levels to amounts that were usual for them and fast for 12 hours overnight (not consuming any food or drink, except water). Upon waking, participants also collected a first morning void (FMV) urine sample.

Participants attended the research unit at 8 am on day 1 (Monday) of each study period. Upon arrival, blood pressure, height and body weight were measured. A fasted capillary blood sample (OneDraw) was also self-collected and participants were set up with the wearable camera (which was worn continuously except if participants used bathroom) before being provided with breakfast. Habitual diet was recorded using the eNutri tool (4-week version). With the exception of mealtimes, participants had the rest of the day as free time but remained in the research unit. At the end of the study day (6 pm), participants were provided with bottled water and a snack for the evening, urine kits (for last evening void (LEV) and FMV samples) and a reminder checklist/log. Days 2-4 repeated day 1 except: 1) Intake24 was used on days 2-4 to record dietary intake during the previous 24 hours, 2) 4-day version eNutri was repeated at the end of day 4 (Thursday) to record dietary intake during the previous 4 days, and 3) capillary blood samples were not collected on day 3 (Wednesday). On day 5 (Friday), participants collected a final FMV, completed Intake24 and returned samples/equipment to the research unit.

Participants’ compliance to the study protocol was recorded by study investigators during the times when they were in the controlled environment. For the times spent outside the research unit, compliance was measured using sample/data collection records and self-reported deviations to study menus.

### Objective dietary assessment tools

Spot urine samples

Participants collected spot urine samples using previously described methods.
^
21
^ For each collection, participants were provided with four additive-free vacuum collection tubes (4 ml) (plus two spares), urine transfer straws and a disposable collection cup (
Figure 2). Participants collected their FMV urine and LEV urine for all four study days in each study period as well as a FMV sample on day 5 and LEV on evening before day 1 using the collection cup. Participants would then transfer samples to four tubes via the transfer straw and store at 4 °C. During each study day, samples were processed in the research unit using previously described methods to render them acellular then they were stored at -80 °C until the end of the study.
^
26
^

**Figure 2. f2:**
[figure not shown]
Urine transfer and straw kit.

Urinary biomarkers of dietary intake will be measured at Aberystwyth University using a combination of Ultra-High Performance Liquid Chromatography (UHPLC) Triple Quadrupole Mass Spectrometry (QqQ-MS) and high-resolution mass spectrometry (HRMS). Previous studies have determined a list of dietary intake biomarkers that reflect intake of common UK diet components and are sufficiently robust and reproducible in spot urine samples from dietary intervention studies.
^
27
^ Spot urine samples are normalised based on specific gravity prior to extraction. Specific gravity correction factors are calculated for urine samples as a fold change of each urine specific gravity to a value of 1.006. Global dietary patterns will be assessed by measuring the urine samples using Proton Nuclear Magnetic Resonance (
^1^H-NMR) at Imperial College London. A global dietary score will be generated from the 1H-NMR urinary metabolic profiles following a previously validated methodology
^
28
^ that will indicate the quality of the diet in combination with a complementary set of urinary dietary biomarkers.

Capillary blood samples

Capillary blood samples were self-collected by participants prior to breakfast on days 1, 2 and 4 using a OneDraw kit (Drawbridge, Thorne Research, Summerville SC, US) as shown in
Figure 3. The single-use device attaches to the upper arm or thigh via a hydrogel adhesive and vacuum and collects 150 μl of capillary blood with little discomfort for the participant. The capillary blood is directly collected onto two paper strips.
^
22
^ When the collection is finished, the cartridge containing the blood samples is placed in the transport sleeve then left at room temperature for at least 48 hours to allow the blood to dry prior to storage at -80 °C.

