### Primary and secondary outcomes to be measured

The primary outcome will be the accuracy of dietary reporting, measured at the end of each intervention week using the known quantities of consumed foods given to participants during the intervention days and dietary data collected from wearable cameras, spot urine samples, capillary blood samples, and self-reported dietary assessments.

Secondary outcome measures include: 1) the creation of a multiplatform model of dietary intake using g/day measured from wearable cameras and self-report dietary assessments, and μg/ml of dietary exposure biomarkers from spot urine samples and capillary blood samples at the end of the study, and 2) the design of a dietary intake study in a free-living population that will be informed by the results of the current dietary intake study protocol.

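### As written, the urine correction factor is a ratio of specific gravity itself to 1.006, which would leave spot-urine dilution almost uncorrected in the mass-spectrometry biomarkers

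*Protocol article*

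**What the plan says.** The rule is in the protocol article under Objective dietary assessment tools, Spot urine samples, in the text after Figure 2 on the mass-spectrometry measurement of urinary biomarkers. It first says: "Spot urine samples are normalised based on specific gravity prior to extraction". It then defines the factor: "Specific gravity correction factors are calculated for urine samples as a fold change of each urine specific gravity to a value of 1.006". No formula is printed, no term for SG minus 1 appears, and neither sentence carries a citation. No other dilution correction (creatinine, osmolality or urine volume) is named.

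The samples are first morning voids (FMV) and last evening voids (LEV): "Participants collected their FMV urine and LEV urine for all four study days in each study period".

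Primary and secondary outcomes to be measured lists, among the sources for the primary outcome, "dietary data collected from wearable cameras, spot urine samples, capillary blood samples, and self-reported dietary assessments". The secondary multiplatform model takes the biomarkers as concentrations: "μg/ml of dietary exposure biomarkers from spot urine samples and capillary blood samples at the end of the study".

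**The concern.** A spot-urine concentration depends on how much of a compound is excreted and on how much water it is excreted in. The correction is there to remove the second part. Water has SG 1.000 by definition, so the dissolved content shows up in the excess over 1, and the fold change that matters is the one in SG - 1. A fold change in SG barely moves, because every urine has an SG just above 1.

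If the rule were followed as printed, urine concentrations would carry dilution noise unrelated to intake. The Statistical analysis section tests agreement with Lin's concordance correlation coefficient, which falls with any such scatter. The urine tool could then look less accurate than it is, in a study meant to compare tools. Anyone repeating the method from the article would have the same problem.

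**Working it through.** **Inputs**

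- Reference SG: 1.006 (Spot urine samples section).
- Literal factor: SG/1.006, or its inverse 1.006/SG. The article does not say which way the factor is applied.
- Comparison factor: (SG - 1)/(1.006 - 1) = (SG - 1)/0.006. This assumes that dissolved content is proportional to SG - 1.
- SG range: not given in the article. I assume 1.003 to 1.030 and also show 1.001 to 1.040.

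The article states no range of correction factors, so there is no figure of its own to reproduce.

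**Step 1. Size of each factor**

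| SG | SG/1.006 | (SG - 1)/0.006 |
|---|---|---|
| 1.001 | 0.995 | 0.167 |
| 1.003 | 0.997 | 0.5 |
| 1.010 | 1.004 | 1.667 |
| 1.020 | 1.014 | 3.333 |
| 1.030 | 1.024 | 5.0 |
| 1.040 | 1.034 | 6.667 |

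Over the wider range the literal factor changes a value by -0.5% to +3.4%. The inverse runs from 1.005 to 0.967, so the direction of the ratio makes no practical difference to its size.

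**Step 2. Dilution left between two samples**

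Take two urines that differ only in dilution.

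- Ratio before correction: (SG_hi - 1)/(SG_lo - 1).
- Ratio after dividing each by its literal factor: the ratio before, divided by SG_hi/SG_lo.
- Share of the log-scale difference removed: ln(SG_hi/SG_lo) / ln(ratio before).

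| SG pair | Before | After literal rule | Log share removed |
|---|---|---|---|
| 1.002 and 1.035 | 17.5 | 16.94 | 1.1% |
| 1.003 and 1.030 | 10.0 | 9.74 | 1.2% |
| 1.005 and 1.030 | 6.0 | 5.85 | 1.4% |
| 1.010 and 1.025 | 2.5 | 2.46 | 1.6% |

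For the second row: 0.030/0.003 = 10.0; 1.030/1.003 = 1.0269; 10.0/1.0269 = 9.74. Dividing instead by (SG - 1)/0.006 brings every ratio to 1.0 under the proportionality assumption.

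**Step 3. Spread over many samples**

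With SG drawn evenly from 1.003 to 1.030 (an illustration, not trial data), the standard deviation of log dilution is 0.588 before the literal correction and 0.580 after it.

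**The case against.** The strongest reply is that the sentence is shorthand. The article prints no formula. Normalising before extraction suggests that the sample itself is adjusted, and a target as low as 1.006 fits diluting concentrated urines to a common level. An adjustment of 1.4% at SG 1.020 would be a step without purpose. The sampling section also relies on previously described methods, and the full study protocol is deposited elsewhere and not shown. This makes the sensible reading plausible. It does not rescue the text: the article does state a rule, and the quantity it names is specific gravity, not its excess over water.

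A reader might infer that the laboratory applied the wrong factor, or that dilution therefore remains in every biomarker concentration. The documents support neither. The article does not show which ratio was used. The sentence belongs to the mass-spectrometry biomarkers, and the 1H-NMR score follows its own cited method, with no word on whether this correction applies to it. The blood, camera, Intake24 and eNutri data are not affected.

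The consequence should not be overstated either. A tenfold difference comes from the ends of an assumed SG range. The Study diets section makes bottled water available through the day, but it also limits evening intake: the take-home water was for use before 8 pm, with nothing further to eat or drink until the return next day. Nothing in the article allows dilution noise to be weighed against the difference between the diets, so it cannot be said that real diet differences would be hidden.

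**Conclusion.** The factor is wrong as written. Used literally, it alters values by about 3% at most and removes only 1 to 2% of the log-scale dilution difference between spot samples. That smallness holds for any plausible SG range and for either direction of the ratio. The contrast of 0.997 to 1.024 against 0.5 to 5.0 depends on the assumed range of 1.003 to 1.030 and on dissolved content being proportional to SG - 1.

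The effect on the trial is conditional. If the laboratory used the literal ratio, the mass-spectrometry urine biomarkers enter the primary outcome essentially uncorrected for dilution, and no other correction is named as a backstop. If it used a ratio on SG - 1, only the description is at fault.

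**What to change.** State the factor as F = (SG - 1)/(1.006 - 1) and say how it is applied: the sample is diluted F-fold, or the measured concentration is divided by F. The direction matters. At SG 1.020, F is 3.33, and multiplying by it would make the dilution bias worse. Samples below 1.006 cannot be diluted to the target and should be scaled up numerically by the same division; at SG 1.003, F is 0.5 and the concentration doubles.

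Confirm with the laboratory which version was applied, and state whether the correction also covers the 1H-NMR score. If the literal ratio was used, undo it and divide by F before the agreement analysis. Where values had been divided by SG/1.006, for example, the corrected value is the reported value × (SG/1.006) / F.

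The cost is one formula in the text and one query. Any rescaling is a computation on SG values that must already exist if factors were calculated. The Study status section says samples have been transferred and analysis is in progress, so the query is best made now.
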